## Aims

Our primary aim is to evaluate the effectiveness of a teacher training programme to teach the mindfulness programme “On Top of Everything” as part of regular classroom teaching in Danish upper secondary schools and schools of health and social care on students’ self-reported mental well-being 6 months from baseline. Secondary aims are (1) to evaluate the effectiveness in a vulnerable subgroup as well as in the total population of students 3 and 6 months from baseline using other outcome measures on mental health and (2) to investigate the facilitators and barriers among teachers to implement mindfulness in schools.

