## Hypothesis

We hypnotise that young people in the intervention group will improve their mental health during the intervention. We expect to find small effect sizes in the total population of students and higher effect sizes in a vulnerable subgroup [13].

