### Sample size

We assume a 1-point increase between-group effect in SWEMWBS to be of public health relevance [44, 45]. From another study that analysed the intervention effect on SWEMWBS in a mixed model with three repeated measurements, and where cluster levels of teacher and school were taken into account, we found a within-person SD = 2.4. To detect an effect on 1 score point in SWEMWBS change, SD = 3.5 = SQRT (2) × 2.4 with 80% power, will require 194 participants in each group, 388 participants in total.

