### Statistical methods

Quantitative data will be analysed according to the intention-to-treat principle using a repeated measurement model with the systematic effect: gender, age, class, time (three time points), intervention, interaction between time and intervention, and random effect of school, teacher/class within school, and student within class. Confidence intervals and standard errors will be found by bootstrapping to adjust for possible deviation from the normality of the random effects. Exploring subgroup analysis will be conducted on gender, a vulnerable subgroup (the 15% with the lowest SWEMWBS score), and type of school. To take account of missing data, we will perform four sensitivity analyses representing scenarios with data not missing at random. Missing outcomes will be substituted with the model-based prediction adding or subtracting 0.02 SD in the intervention or control arm.

Qualitative data will be transcribed and analysed based on qualitative content analysis. Each focus group interview will be read and notes will be taken, and themes will be introduced, organised, and related to quotes that are open to interpretation and that continue to an analytic investigation and connection of themes and quotes from all focus group interviews.

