### Trial status

In total, 43 schools and 76 teachers consented to participate in the trial (44 teachers from 30 upper secondary schools and 32 teachers from 13 schools of health and social care). Teachers have recruited approximately 1100 students. Three focus group interviews were conducted among teachers in the intervention group after the implementation of the “On Top of Everything” programme.

Teaching of the “On Top of Everything” programme among students in the intervention group took place during the spring semester of 2021. Interviews among teachers took place in June 2021. The last quantitative data (6-month follow-up) were collected among students in the autumn of 2021. We will start cleaning and analysing the data at the beginning of 2023.

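### The hypothesis of a larger effect in vulnerable students has no stated test; a continuous baseline interaction would test it with more power than a 15% cut

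*Protocol article*

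**What the plan says.** Under Hypothesis, the protocol article makes a comparative statement: "We expect to find small effect sizes in the total population of students and higher effect sizes in a vulnerable subgroup". Under Aims, secondary aim 1 is not comparative: "to evaluate the effectiveness in a vulnerable subgroup as well as in the total population of students 3 and 6 months from baseline".

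Statistical methods gives the fixed part of the repeated measurement model as "gender, age, class, time (three time points), intervention, interaction between time and intervention", with random effects for school, teacher or class, and student. The subgroup work is one sentence: "Exploring subgroup analysis will be conducted on gender, a vulnerable subgroup (the 15% with the lowest SWEMWBS score), and type of school". Within it, vulnerability is defined only by the words "a vulnerable subgroup (the 15% with the lowest SWEMWBS score". It does not say how a subgroup analysis is carried out. No term or contrast that compares vulnerable students with others is named.

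The outcome table describes SWEMWBS as the sum of seven items scored 1 to 5. It is collected at baseline, 3 months and 6 months, so every baseline responder has a numeric baseline score.

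**The concern.** A claim that the effect is larger in one group than in the whole population needs a comparison of effects. An estimate inside the subgroup does not supply it. A significant result among the lowest 15% is compatible with the same effect everywhere, and a non-significant one is compatible with a real gradient, because the subgroup is small. Readers will set the subgroup figure beside the overall figure and draw the comparison by eye.

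The choice of scale adds to this. Vulnerability is defined by cutting the score that is also the primary outcome, although the uncut score is available. If the effect rises steadily as baseline well-being falls, the cut discards information that the trial already holds. What is at stake is whether the trial can confirm or refute its own stated expectation; the primary analysis is not at issue.

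**Working it through.** **Inputs from the protocol article**
- Trial status: "Teachers have recruited approximately 1100 students".
- Sample size: "We assume a 1-point increase between-group effect in SWEMWBS to be of public health relevance", and "SD = 3.5 = SQRT (2) × 2.4 with 80% power, will require 194 participants in each group, 388 participants in total".
- Statistical methods: the subgroup fraction of 15%.

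**Assumptions, not in the document:** two-sided alpha of 0.05, equal arms, a normal baseline score, effect modification linear in that score, no clustering, no dropout.

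**The plan's own figure.** n per group = 2 × (1.96 + 0.84)² × 3.5² / 1² gives 193 by the normal formula. The t-based solution is 193.3, rounded up to 194. The stated 194 reproduces with the rounded SD of 3.5 (√2 × 2.4 is 3.39), so 3.5 is used below.

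**1. Subgroup estimate alone**
- Size: 0.15 × 1100 = 165 students, or 165/43 ≈ 4 per school.
- SE = 3.5 × √(4/165) = 0.545.
- Power for 1 point = Φ(1/0.545 − 1.96) = 45%.
- This is power to show some effect in the subgroup, not a larger one.

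**2. Lowest 15% against the other 85%**
- SE in the other 935 students = 3.5 × √(4/935) = 0.229.
- SE of the difference = √(0.545² + 0.229²) = 0.591.
- Power for a 1-point gap = Φ(1/0.591 − 1.96) = 39%.
- The hypothesis sets the subgroup against the total population. That difference is 0.85 times the difference from the rest, so the test is the same.

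**3. Interaction with the continuous baseline score**
- The 15% point of a normal score is z = −1.036, with density 0.233.
- Mean of the lowest 15%: −0.233/0.15 = −1.554. Mean of the rest: 0.233/0.85 = 0.274. Distance: 1.829 SD (unrounded inputs).
- A 1-point gap spread linearly is 1/1.829 = 0.547 points per baseline SD.
- SE of that slope = 2 × 3.5/√1100 = 0.211.
- Power = Φ(0.547/0.211 − 1.96) = 74%.

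A simulation of 4000 trials gave 38% for step 2 and 74% for step 3.

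**4. Information kept by the cut.** 0.233²/(0.15 × 0.85) = 0.43. This ratio does not depend on the SD or the sample size.

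**5. Precision of the effect in vulnerable students.** The effect predicted by the linear model at the subgroup's mean score has variance proportional to 1 + 1.554² = 3.416. The subgroup-only estimate has 1/0.15 = 6.667. The ratio is 0.51. At the 15th percentile itself it would be (1 + 1.036²)/6.667 = 0.31, but that is the upper edge of the group and a different quantity.

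**Clustering.** The article gives no intraclass correlation. Assuming 0 to 0.05 and 1100/76 ≈ 14.5 students per class, the design effect is 1.00 to 1.67 for all students and 1.00 to 1.06 for the subgroup. At 0.05, the 0.51 becomes (1.67 + 2.415)/(6.667 × 1.06) ≈ 0.58 if only the main-effect part is inflated, and 3.416 × 1.67/(6.667 × 1.06) ≈ 0.81 if all of it is.

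**The case against.** The strongest reply is that the article does not say how the subgroup analyses are done. The listed terms describe the main model. A stratified fit and an interaction term are both compatible with the text, and an analysis plan that is not shown may name one. This stands: a reader might infer that the plan rules out a comparative test, and the document does not support that. What remains is that the article states both a comparative hypothesis and a list of model terms, and nothing it states links them. If an interaction is intended on the 15% cut, step 2 shows its weakness.

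Other stronger readings also fail:
- **That secondary aim 1 is left unanswered.** The aim asks for effectiveness within the subgroup, which a subgroup estimate provides.
- **That the subgroup's effect will look inflated.** Selecting the lowest 15% of a normal score shrinks its baseline SD to 0.44 of the total, so an identical point effect would look 2.3 times larger if divided by that SD. The article nowhere proposes to do so, and its sample size works in score points.
- **That the subgroup result will decide who is offered the programme.** The article presents a population-based strategy delivered in ordinary classes.
- **That the cut always discards most of the information.** This holds for linear modification. If the effect truly changes at a threshold near the 15% point, the cut is the better choice.

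The analysis is also labelled exploratory, which limits the consequence.

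**Conclusion.** The point holds in limited form. The hypothesis is comparative, and the article states no comparison that would test it. The planned subgroup estimate serves aim 1 only.

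In size, a continuous interaction has roughly twice the power of a 15/85 contrast for the same 1-point gap (74% against 39%), because the cut keeps about 43% of the information. These figures rest on linear modification, a normal baseline score, SD 3.5, 1100 students, and no clustering or dropout. Dropout would lower both power figures, and clustering changes them by an amount the document does not allow one to calculate. The 43% itself needs only linearity, normality and the absence of clustering. This is an inexpensive improvement to a secondary, exploratory question and is worth making. It does not bear on the validity of the primary result.

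**What to change.** Name a test of the hypothesis:
- Fit the 3- and 6-month SWEMWBS scores with baseline SWEMWBS as a continuous covariate, its interaction with intervention by time, and the same random effects. This should be a separate model. In the main model baseline is one of the three outcome times, so a three-way term with baseline does not fit there.
- Report the interaction with its confidence interval. Also report the predicted 6-month effect at the mean baseline score of the lowest 15%, pooled over arms.
- Check linearity with a spline.

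Keep the lowest-15% estimate as a descriptive answer to aim 1. Define it by one cut on the baseline score, pooled over arms and set at a whole score before arms are compared, since an integer sum will seldom split at exactly 15%. Report effects in points or in total-sample SD.

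The cost is one extra model on data already collected. The downside is the linearity assumption, which the spline and the retained subgroup estimate help to check.

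### The 0.02 SD shift in the four not-missing-at-random analyses is too small to test robustness to informative non-response

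*Protocol article*

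**What the plan says.** Under Statistical methods, the protocol article says of missing data that "we will perform four sensitivity analyses representing scenarios with data not missing at random". It then gives the rule: "Missing outcomes will be substituted with the model-based prediction adding or subtracting 0.02 SD in the intervention or control arm". It does not say which SD is meant, why 0.02 was chosen, or whether any larger shift will be tried. The same paragraph says that standard errors and confidence intervals will be obtained by bootstrapping.

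The scale for judging the shift comes from Sample size. The target is given as "We assume a 1-point increase between-group effect in SWEMWBS to be of public health relevance". The SDs are given as "we found a within-person SD = 2.4" and "SD = 3.5 = SQRT (2) × 2.4 with 80% power", and the calculation "will require 194 participants in each group, 388 participants in total". Under Trial status the article reports that "Teachers have recruited approximately 1100 students".

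**The concern.** A shift analysis for data not missing at random is useful only if the shift is large enough to represent a departure that could matter. Here the shift is a small fraction of the relevant effect, and it applies only to the students whose outcome is missing. The four scenarios then sit almost on top of the missing-at-random analysis that they are meant to challenge.

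The design makes the question a fair one. Outcomes are self-reported, neither students nor providers are blinded, and students opt out by leaving questionnaires unanswered. Classes were enrolled after schools had been randomised. Teaching took place in spring 2021 and the last follow-up was in autumn 2021. Non-response that depends on both arm and well-being is therefore possible, and these four analyses are the only check on it that the article describes. At stake is what the trial can say about robustness, not the primary estimate itself.

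**Working it through.** **Inputs from the article.** Shift 0.02 SD (Statistical methods). Within-person SD 2.4, SD of change 3.5, target 1 point, 80% power, 194 per group (Sample size). About 1100 students (Trial status), taken as about 550 per arm.

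**Assumptions.** The missing fraction *p* is not stated and is varied. Alpha is not stated and is taken as two-sided 0.05. Equal arms are assumed, and a design effect of 2 is used where stated.

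**1. The plan's own figure.** n per group = 2 × (1.96 + 0.842)² × 3.5² / 1² = 192.4, rounded up to 193. The t-distribution version gives 193.3, rounded up to 194, which matches the article. The stated root, √2 × 2.4, is 3.39 and would give 181, so 3.5 is the SD actually used. It is used below; the smaller SD makes every shift smaller.

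**2. Shift per missing value.**
- SD 2.4: 0.02 × 2.4 = 0.048 points.
- SD 3.5: 0.02 × 3.5 = 0.07 points.

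This is about 5% to 7% of the 1-point target.

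**3. Movement of the 6-month contrast.** One arm shifted: 0.02 × SD × *p*. Arms shifted in opposite directions: twice that. With SD 3.5:

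| Missing per arm | One arm | Opposite shifts |
|---|---|---|
| 20% | 0.014 | 0.028 |
| 30% | 0.021 | 0.042 |
| 50% | 0.035 | 0.070 |
| 100% (limit) | 0.070 | 0.140 |

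With an assumed SD of 5.0 and 30% missing, the figures are 0.03 and 0.06.

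**4. Against the standard error.** SE = 3.5 × √(2/n).
- 194 per arm: SE 0.355. At 30% missing the shift is 0.021/0.355 = 0.06 SE, or 0.042/0.355 = 0.12 SE.
- 550 per arm, no clustering: SE 0.211. The shift is 0.10 or 0.20 SE.
- 550 per arm, design effect 2: SE 0.298. The shift is 0.07 or 0.14 SE.

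**5. Effect on the p-value** (30% missing, one arm, across these three SEs). An estimate at z = 2.5 goes from p = 0.012 to 0.015–0.016. An estimate exactly at 0.050 goes to 0.057–0.063. Across one-arm and opposite shifts, the chance of landing in the narrow band where significance is lost is about 0.1% to 3% if the true effect is 1 point, and about 2% to 8% if it is 0.5 points.

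**6. Tipping point.** This is the one-arm shift, in SD units, that brings the lower 95% limit of a 1-point estimate to zero: (1 − 1.96 × SE) / (*p* × SD). At 30% missing the denominator is 0.3 × 3.5 = 1.05.
- 194 per arm: (1 − 0.697)/1.05 = 0.29 SD.
- 550 per arm: (1 − 0.414)/1.05 = 0.56 SD.
- 550 per arm, design effect 2: (1 − 0.585)/1.05 = 0.40 SD.

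These are about 14 to 28 times 0.02. The SE here is not enlarged for the lost data. If only 70% of students contribute (135.8 or 385 per arm), the SE is 0.425 or 0.252. The tipping points then become (1 − 0.833)/1.05 = 0.16 SD and (1 − 0.494)/1.05 = 0.48 SD, still at least eight times the planned shift.

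**The case against.** **It is only a sensitivity analysis.** This stands. The primary model, outcome and estimate are unaffected, which limits the severity. The article also describes two reminders, access for absentees and completion in school hours, and it gives no evidence of differential non-response.

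**The four scenarios can be read in two ways.** The wording fits plus or minus in one arm at a time, or all sign combinations across both arms. The article does not settle this, so both are shown. The one-arm reading halves the largest movement and makes the check weaker still.

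**No scenario can ever change the result.** A reader might infer this, but it goes too far: an estimate within about 0.02 to 0.04 points of the significance boundary could cross it (30% missing, SD 3.5). That would be chance proximity, not a test of robustness. Nor does the article say that robustness will be claimed whatever happens; that would be a guess about reporting. And no shift of any size detects informative non-response. It only shows how far the conclusion depends on an assumed departure.

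**Substituting predictions makes the standard errors too small.** A reader might infer this too, but the article does not establish it. Standard errors come from bootstrapping, and the order of imputation and resampling is not stated. In a simplified check (500 students, total SD 4, no clustering; all assumptions), a fixed prediction recomputed in each bootstrap sample gave an SE of 0.330 against a true 0.321 at 30% missing. Imputing once before resampling gave 0.230. So understatement depends on a step that an article may leave to the full plan.

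**Conclusion.** The point holds: the fixed value of 0.02 SD cannot do the job the article assigns to it. The contrast would move by 0.014 to 0.035 points with one arm shifted and 20% to 50% missing, or 0.028 to 0.070 with opposite shifts, against a target of 1 point. Even the impossible limit of 100% missing gives 0.14 points.

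This rests on SD 3.5, on an assumed missing fraction, and on the shift being applied to 6-month outcomes. Using SD 2.4, an assumed SD of 5.0, either reading of the four scenarios, or an assumed design effect of 2 does not change the conclusion. Whether 0.02 is a misprint cannot be settled from the document. The value should be corrected before analysis, but it does not endanger the primary result.

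**What to change.** 1. Confirm whether 0.02 is intended, and correct it if it is a misprint.
2. Name the SD to which the shift refers, and state which arm and sign each scenario uses.
3. Before analysis, replace the single value with a range of shifts, in each arm and each direction, that extends to the tipping point, and report that point. The figures in the working show the region to cover: about 0.3 SD at 194 per arm and about 0.56 SD at 550 per arm for a 1-point estimate with 30% missing in one arm, ignoring clustering. The final range should use the observed missing fraction and standard error.
4. State that imputation is redone within each bootstrap sample, so that the intervals carry its uncertainty.

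The cost is a few sentences and a few more model runs. The range, or the rule that sets it, should be fixed before outcomes are compared by arm, because a shift chosen after the results are known would carry little weight.

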#### Significance and potential impact of the project

This trial will estimate the effectiveness of a population-based strategy on mental health in Danish young people enrolled in education. It will investigate the effectiveness of a mindfulness-based intervention based on the well-described MBSR programme modified to young people by the Danish Center for Mindfulness, Aarhus University. Furthermore, it will investigate facilitators and barriers among teachers to implement mindfulness in schools.

### Trial status

In total, 43 schools and 76 teachers consented to participate in the trial (44 teachers from 30 upper secondary schools and 32 teachers from 13 schools of health and social care). Teachers have recruited approximately 1100 students. Three focus group interviews were conducted among teachers in the intervention group after the implementation of the “On Top of Everything” programme.

Teaching of the “On Top of Everything” programme among students in the intervention group took place during the spring semester of 2021. Interviews among teachers took place in June 2021. The last quantitative data (6-month follow-up) were collected among students in the autumn of 2021. We will start cleaning and analysing the data at the beginning of 2023.

### Dissemination of knowledge

The results will be submitted for publication in international peer-reviewed journals. The results will also be presented at national and international conferences and scientific meetings. We also attempt to communicate the results in the press and specialist journals, and we will communicate the results at webpages, LinkedIn profiles, and social media (Facebook and Instagram).

## Data Availability

The dataset will be available from the second author by reasonable request after publication.

## Abbreviations

BRS: Brief Resilience Scale
DASS: Depression Anxiety Stress Scale
EQ: Experiences Questionnaire
HRQoL: Health-related quality of life
MBSR: Mindfulness-based stress reduction
PSS: Perceived Stress Scale
REDCap: Research Electronic Data Capture
SDQ: Strengths and Difficulties Questionnaire
T-ILS: Three-Item Loneliness Scale
SWEMWBS: Warwick-Edinburgh Mental Well-Being Scale: the short version
WHO: World Health Organization
WHO-5: 5-Item World Health Organization Well-Being Index
